# Dissemination of an evidence-based motivational interviewing brief intervention for substance use disorders to HIV service organizations across the United States: protocol for a national-level cluster-randomized adaptive parallel-groups superiority experiment

**DOI:** 10.1186/s13722-025-00612-8

**Published:** 2025-10-23

**Keywords:** Dissemination, Exploration, Adoption, Facilitation, HIV, Substance use disorders, Motivational interviewing, Brief intervention

## Abstract

**Background:**

Given the high prevalence of substance use disorders (SUDs) among people with HIV, integration of evidence-based SUD services within HIV service settings is needed. Federally-funded training and technical assistance centers, such as the Health Resources and Services Administration-funded AIDS Education and Training Center (AETC) network, are part of the support system that deliver strategies to promote the uptake of evidence-based interventions. Previously, our program of research supported (1) the effectiveness of facilitation for improving both the implementation and effectiveness of a motivational interviewing-based brief intervention for SUDs in HIV service organizations (HSOs), (2) motivational interviewing as having the best setting-intervention fit for HSOs, and (3) distributing educational materials as having the best setting-strategy fit for AETCs. Because exploration and adoption/preparation are phases that must occur before implementation and sustainment, we seek to test the effectiveness of facilitation to augment an initial distributing educational materials dissemination strategy.

**Methods:**

Using a multi-cohort cluster-randomized adaptive parallel-groups superiority experiment design, our aim is to test the effectiveness of augmenting a standard distributing educational materials dissemination strategy with a brief exploration facilitation dissemination strategy to support implementation of a motivational interviewing-based brief intervention. For each rollout, HSOs not responding to the distributing educational materials strategy will be randomized to either (a) receive no further intervention or (b) receive the exploration facilitation strategy. Assessed 4-months post-dissemination, the primary dissemination outcome is organizational-level adoption/preparation of the intervention (i.e., 1 + HSO staff downloads the manual and/or enrolls in the online asynchronous training). The secondary dissemination outcome is organization-level exploration of the intervention (i.e., 1 + HSO staff opens the dissemination email).

**Discussion:**

Before evidence-based interventions are implemented in practice to improve health outcomes, they must first be successfully disseminated and then explored and adopted by service organizations and providers. Because training and technical assistance centers have limited resources for dissemination efforts, effective adaptive dissemination strategies that utilize limited resources are needed. If we find the exploration facilitation strategy to be an effective adjunct to the distributing educational materials strategy, we hope that this adaptive dissemination strategy can be widely adopted and implemented by training and technical assistance centers.

**Trial registration:**

Open Science Framework: https://osf.io/urgzd. Registered 1/30/2025.

**Protocol version:**

1/30/2025 Version 1.

**Supplementary Information:**

The online version contains supplementary material available at 10.1186/s13722-025-00612-8.

## Background

People with HIV are at elevated risk of developing substance use disorders (SUD), with some estimates indicating nearly 50% of people with HIV have a SUD [1]. This prevalence rate is six times greater than the general United States adult population [2]. HIV service organizations (HSOs) are diverse in the services that they provide for people with HIV, with some largely providing clinical care and others largely providing case management focused on social determinants of health. HSO staff have reported high rates of specific SUDs among their clients, ranging from 28% for cocaine use disorder to 42% for alcohol and cannabis use disorders [3]. These rates are particularly concerning because SUDs negatively impact the HIV care continuum, including retention in HIV care, medication adherence, and viral load suppression [4–6].

Given these high rates of SUD, evidence-based interventions (EBIs) for SUD need to be integrated in settings that serve people with HIV [7–9]. However, scaling up EBIs requires attention to factors at the organizational and systems level. Organizational change theories and implementation science frameworks point to the importance of the fit between an EBI and the setting in which it is to be implemented [10–14]. However, setting-intervention fit has often been overlooked [15], which may impede dissemination and implementation efforts. Recently, setting-intervention fit for SUD service integration was studied through a stakeholder-engaged real-time Delphi of 202 HSOs. Of nine SUD interventions that included medications and behavioral therapies, motivational interviewing was the most promising EBI in terms of being fundable, implementable, retainable, sustainable, scalable, and timely, indicating setting-intervention fit [16]. Motivational interviewing is a patient-centered counseling approach that utilizes a facilitative style to help patients resolve ambivalence about behavior change [17]; compared to no treatment, motivational interviewing reduces substance use [18].

Of note, motivational interviewing has been adapted for the HSO setting. In a dual-randomized type 2 hybrid trial, Garner et al. [19] supported the effectiveness of a motivational interviewing-based brief intervention (MIBI) for clients with comorbid HIV and SUD. This trial also compared two implementation strategies, which are methods and techniques that help organizations to adopt and implement EBIs [20]. All HSOs received training, feedback, and consultation. Half of the HSOs also received facilitation, which is an implementation strategy that uses a process of interactive problem solving; it often involves an external facilitator who works with agency staff to identify supports for implementation efforts and strategies to overcome barriers [21]. Adding facilitation to a staff-focused training, feedback, and consultation strategy yielded greater implementation effectiveness, defined as quality and consistency, than training, feedback, and consultation [19].

Given evidence of the MIBI’s effectiveness and its setting-intervention fit, a key question is how to effectively disseminate this EBI to HSOs [22–25]. Dissemination, “the active approach of spreading evidence-based interventions to the target audience via determined channels using planned strategies” [26] (p. 339), is critically important to integrating EBIs and improving health outcomes [24, 27]. Dissemination strategies are most relevant during the early phases of moving an EBI into practice. The EPIS (exploration, adoption/preparation, implementation, sustainment) framework characterizes this process [28]. In the exploration phase, an organization realizes that their clients have an unmet need and considers EBIs to meet that need. Over time, an organization may move into the adoption/preparation phase, which entails identifying implementation strategies (e.g., training) to support EBI delivery [23]. Dissemination strategies that focus on raising awareness of an EBI and availability of training may help organizations to move through these early phases.

A critical issue for scaling up EBIs is identifying effective dissemination strategies that can be utilized by existing entities that support dissemination and implementation efforts. As seen in Fig. 1, according to the Interactive Systems Framework for Dissemination and Implementation [29–31], intermediaries and purveyors of EBIs can play important roles in dissemination and implementation efforts. In the United States, there are federally-funded training and technical assistance centers, which provide training on EBIs as well as other implementation strategies [31]. It is important to design dissemination strategies that can accelerate EBI exploration and adoption/preparation while being feasible for training and technical assistance centers to provide.

For HSOs in the U.S. and its territories, the Health Resources and Services Administration (HRSA)-funded AIDS Education and Training Centers (AETC) are a support system that provide training and technical assistance. A recent real-time Delphi survey of 64 AETC representatives sought to identify the most promising dissemination and implementation strategies [21] using a setting-strategy fit index [32]. For each of ten strategies, representatives rated importance, feasibility, readiness, scalability, pressure to offer, and need. The strategies with the highest setting-strategy fit were distributing educational materials and providing access to asynchronous training.

This article describes the protocol for MOTIVATE CHANGE (Motivational Outreach and Training Interventions for Vulnerable Affected Targeted Empowerment, and Counseling for HIV-positive clients with Addiction Needs for Guidance and Education), a national-level cluster-randomized adaptive parallel-group (1:1 ratio) superiority experiment. The SPIRIT guidelines have been used to structure this protocol [33]. As shown in Fig. 1, the primary aim is to test the effectiveness of augmenting an initial distributing educational materials strategy (i.e., an email with key messages about the MIBI and an invitation to a website with access to a MIBI manual and other training resources upon enrollment) with a brief exploration facilitation strategy. The exploration facilitation strategy utilizes a trained facilitator who leads an agency representative through a discussion of supports and barriers to implementing the MIBI while addressing ambivalence about implementation using a supportive interpersonal style. For HSOs not responding to the initial strategy, the HSO (and its staff) will be randomized to receive either (a) an exploration facilitation strategy or (b) no further intervention. Distributing educational materials was selected as the control strategy because it had the greatest setting-strategy fit in our survey of AETCs [32]. Exploration facilitation was selected as the experimental dissemination strategy based on implementation research supporting it as an effective strategy when used during the preparation, implementation, and sustainment phases [19]. The primary hypothesis is that for HSOs that do not respond to the initial distributing educational materials dissemination strategy, HSO-level MIBI adoption (i.e., HSOs with 1 + staff downloading the MIBI manual and/or enrolling in the online training) will be significantly greater among HSOs assigned to the distributing educational materials plus exploration facilitation condition than HSOs in the distributing educational materials-only condition. As such, this study seeks to help address the need for rigorous research on dissemination strategies, a need most recently underscored by Turon and colleagues [25] as part of their scoping review on dissemination of public health research to prevent non-communicable diseases.

**Fig. 1 Fig1:**
[figure not shown]
Guiding framework (panel A) and conceptual model of aim, hypothesis, and timeline (panel B)

## Methods/design

### Study setting

The MOTIVATE CHANGE dissemination experiment will be conducted by recruiting community-based HSOs and their staff located in the contiguous United States and District of Columbia. HSOs vary in services provided, as some are primarily clinical (e.g., prescribing HIV medications, providing CD4 T-lymphocyte testing and HIV viral load testing), and others are primarily non-clinical (e.g., providing medical and non-medical case management to people with HIV to address social determinants of health).

### Eligibility criteria

A national directory of HSOs developed for two earlier studies was updated to identify potentially eligible HSOs. In 2018–2019, research staff created a comprehensive database of HSOs via publicly existing resources (e.g. HIV.gov, poz.com, thebody.com) and then called each HSO to confirm they were open and update contact information [3]. This process was repeated in 2020 [16] and in 2023 for the current study. HSOs must be open or perceived to be open at the time of the experiment launch and must provide HIV-related services such as case management, direct healthcare, behavioral health services (including to address substance use), or linkage to care. Determinations regarding eligibility are made based on organizational websites. HSOs without a functional website are considered “closed” and excluded. HSOs that had previously participated in the SAT2HIV or SAT2HIV-II studies, which focused on implementation strategies for the MIBI, are excluded (*n* = 43).

For eligible HSOs, organizational websites are searched to identify email addresses of staff members who interact with clients or individuals who make decisions regarding staff training, such as chief executive officers, office administrators, clinic managers, or education/training managers (e.g., leadership, staff, or staff directory sections). Individuals in these roles are added to the study database. To increase the validity and deliverability of the study-related emails, HSO Directory email addresses are evaluated using Bouncer, a paid online email validation service that checks activity and the ability to receive messages. Email addresses deemed deliverable, risky, or unknown are included in the experiment; undeliverable email addresses are excluded.

Provider-level eligibility criteria for MOTIVATE CHANGE are being: (1) a staff member of an agency in the HSO Directory located in the contiguous US states (residents of Alaska and Hawaii are not eligible due to limitations of gift card distribution) or District of Columbia; (2) at least 18 years of age; (3) fluent in English;, and (4) willing and able to provide consent to participate in the study. Any provider who meets inclusion criteria can participate, so there is no pre-set numbers of providers allowed per agency.

### Strategies

An overview of the two dissemination strategies being tested is provided in Table 1 using the Strategies Timeline, Activities, and Rationale (STARationale) Table format. STARationale was recently introduced by Garner et al. [34] to help standardize the specification and reporting of strategies in accordance with recommendations by Proctor et al. [35] and Perez-Jolles et al. [36]. Additional details regarding each strategy, which are delivered by the study team, are provided in the text below and in Table 1.

**Table 1 Tab1:** The strategies timeline, activities, and rationale (STARationale) table for the MOTIVATE CHANGE project

	STRATEGY ACTIVITIES			
**STRATEGY** ***TIMELINE***	**Operationalization** (i.e., name and general description/definition)	**Function** (i.e., purpose and targeted implementation or client outcomes)	**Form** (i.e., a precise description of the activity, delivering actor, and dose)	**STRATEGY** ***RATIONALE***
*1st Strategy*	Distributing educational materials. A staff-focused strategy that seeks to give HSO staff access to MIBI-related educational materials (e.g., manual, online course)	To help HSO staff adopting the MIBI learn how to implement the MIBI with clients that are in need.	An initial email (see Supplemental File 1) and one reminder email, each sent by the research team email.	Powell et al. [28] recommended and Patel et al. [29] found to have the greatest setting-strategy fit.
*2nd Strategy*	Exploration Facilitation. A staff-focused strategy that uses principles of motivational interviewing to help increase the likelihood of MIBI adoption by one or more HSO staff.	To help increase the likelihood of exploration and adoption/preparation by HSO staff who did not respond to the distributing educational materials strategy.	Up to three telephone call attempts by a trained facilitator to engage, focus, evoke, and plan with an HSO staff regarding exploration and adoption/preparation of the MIBI.	Powell et al. [28] recommended and Garner et al. [17, 34–36, 43] supported facilitation as an effective implementation strategy.

Note: AETCs = AIDS Education and Training Centers; HSO = HIV Service Organization; MIBI = Motivational Interviewing-based Brief Intervention

#### Distributing educational materials

All HSOs begin in the distributing educational materials condition and receive the MOTIVATE CHANGE dissemination email (see Supplemental File 1), which has been designed to deliver three key messages: 1) SUD is common among people with HIV; 2) the MIBI, which takes 15–30 min to deliver, reduces substance use; and 3) the study is offering no-cost access to training resources on the MIBI. The dissemination email was developed using feedback from the study’s guiding coalition comprised of experts in HIV and SUD. Rolling batches of HSOs will be constructed for study management purposes. For each batch, HSO staff will be initially emailed on Tuesday. If a staff member from the HSO does not enroll by Friday, a dissemination email reminder will be sent. Email recipients have approximately 30 days to engage with the study’s landing page and enroll in the study by clicking the email’s “Learn More and Enroll” button before their access to the landing page expires. A one-week run-in period will be used to determine the percentage of HSOs for which the distributing educational materials emails is sufficient to move at least one HSO staff from pre-exploration to exploration, defined as at least one staff opening either of the dissemination emails. HSOs with at least one staff member enrolling in the study during the run-in period will not be randomized and will be categorized as a separate group (“immediate exploration”).

HSO staff who click the “Learn More and Enroll” button in the dissemination email will be taken to the study’s landing page to provide electronic informed consent, complete a brief baseline demographics survey, and gain access to Phase I resources for approximately thirty days from the time of the initial email invitation. Phase I resources include the MIBI Manual for self-review and no-cost access to the online course, “A Tour of Motivational Interviewing: An Interprofessional Road Map for Behavior Change” (Tour of MI). The MIBI Manual is a comprehensive guide that outlines the MIBI intervention, provides practical tools for conducting the intervention, and requires less than 90 min to review. Tour of MI is a self-paced, four-hour online course developed by the Mid-America Addiction Technology Transfer Center at the University of Missouri-Kansas City School of Nursing and Health Studies. This course offers foundational training in MI, emphasizing collaborative conversations to strengthen a client’s motivation for behavior change and the use of MI techniques within an atmosphere of acceptance and compassion. The course content is applicable across health professionals. Some professions are eligible for 4.0 continuing education credits for a fee (CE; Continuing Medical Education, Continuing Nursing Education, National Association of Social Workers, and NAADAC); a certificate of completion is available if CEs are not provided. If the participant provides documentation confirming prior completion of the Tour of MI, they will be fast-tracked to Phase II.

In Phase II, staff participants who complete the Tour of MI will receive no-cost access to two online learning platforms (SIMmersion and LYSSN) for 60 days. SIMmersion is an interactive simulation platform that facilitates the development of MI communication skills through practice with virtual role-players simulating SUD-specific scenarios. Participants are provided instant feedback, performance evaluations, and suggestions for improvement by an on-screen virtual coach to help them refine their MI skills. Participants can track their progress and identify areas for development. LYSSN, an AI-driven training platform, provides participants with on-demand practice and feedback on their MI sessions. LYSSN generates transcripts and expert analyses of training sessions, assessing the quality and effectiveness of the MI sessions. The platform offers real-time, actionable feedback based on over 55 fidelity measures. Participants will access SIMmersion and LYSSN through individual accounts managed by the study team.

#### Exploration facilitation

Following the initial one-week run-in period, approximately half of the non-responding HSOs will be randomized to receive the project’s exploration facilitation dissemination strategy. The rationale for testing exploration facilitation as a dissemination strategy is provided by research supporting the effectiveness of the implementation and sustainment facilitation (ISF) strategy [19, 37–40]. For HSOs and their staff randomized to the distributing educational materials + exploration facilitation strategy, an external facilitator on the study team who is trained in ISF Strategy and motivational interviewing (MI) will call the HSO within ~ 10 business days after randomization and attempt to reach a training manager or other appropriate representative. Facilitators will make up to three attempts to contact an appropriate staff member at the HSO and a voicemail may be left requesting a return call. HSO staff will also have the option to schedule a facilitation call if the time of initial contact is not convenient.

The exploration facilitation strategy is estimated to take up to 30 min. The call will begin with an introduction and verbal informed consent. General HSO questions will be asked, such as organizational ownership, number of staff, number of clients with HIV, and current use of SUD screening and SUD interventions. Then, an overview of the MIBI and the study will be provided. The trained facilitator will then lead the participant through an unscripted decisional balance exercise to assess supports and barriers to implementing the MIBI at their HSO. Through this MI-based exercise, facilitators will seek to help participants find the motivation to change the practices at their HSO by addressing ambivalent feelings and uncertainties. The facilitator will resend the original dissemination email to the participant so that prior to expiration they may review the landing page on their own time and proceed to study enrollment if they choose. Access to the training resources remains on the original schedule (i.e., access expires approximately thirty days from the date of the initial email invitation). The facilitator will also encourage the participant to forward the dissemination email to other HSO staff.

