### Outcomes

Guided by the extant literature, our primary dissemination outcome is *adoption*, which Baumann et al. [24] define as occurring when “the individual or organization engages in a number of activities that will lead to the research evidence being integrated into clinical practice and/or policy decisions” (p. 8). Per this definition and our cluster-randomized design, we will examine both *staff-level MIBI adoption* (i.e., number of HSO staff who download the MIBI manual and/or enroll in the online asynchronous MI training) and *organization-level MIBI adoption* (i.e., number of HSOs with staff-level MIBI adoption by 1 + staff). Secondary outcomes are: *staff-level MIBI exploration* (i.e., number of HSO staff who open either dissemination email), *organization-level MIBI exploration* (i.e., number of HSOs with staff-level MIBI exploration by 1 + staff), *staff-level MIBI implementation* (i.e., number of HSO staff who self-report any use of the MIBI with clients at the four-month follow-up survey), and *organization-level MIBI implementation* (i.e., number of HSOs where at least one staff person reports any use of the MIBI with clients at the four-month follow-up survey). Figure 2 illustrates MIBI status progression at the HSO-level. For this study, initial MIBI status will be Pre-Exploration for all HSOs and their staff. Transition to other statuses will be based on information from the project’s enrollment database and four-month follow-up survey using the outcome definitions above.

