Because training and technical assistance centers have limited resources for dissemination efforts, effective dissemination strategies that help them utilize their limited resources most efficiently are needed. The MOTIVATE CHANGE experiment’s adaptive design may help in this regard. By quantifying HSOs’ progress through exploration and adoption/preparation phases for the distributing educational materials strategy, results may help training and technical assistance centers to estimate how much change occurs in the very short-term (i.e., one week) versus a longer period (i.e., four months). Distributing educational materials via email invitations to web-based resources is a low-intensity strategy that should have minimal costs. Exploration facilitation has greater costs because of the time required for training facilitators and then delivering the strategy. However, some efficiency may be gained by targeting exploration facilitation to those HSOs for which distributing educational materials was insufficient, rather than offering exploration facilitation to all HSOs. Using an adaptive approach may save resources, which is important for training and technical assistance centers that often serve a large geographic region but have limited financial resources [46].

We estimate MOTIVATE CHANGE will disseminate the MIBI to approximately 750 HSOs. According to Rogers [14], “a six-month communication intervention might increase knowledge of an innovation on the part of 35% of the audience while influencing only 2 or 3% of the individuals to adopt the new idea” (p. 198). We may then expect our initial distributing educational materials strategy to lead to exploration by 263 HSOs (35% of 750) and adoption/preparation by 15 to 23 HSOs (2–3% of 750). Ideally, MOTIVATE CHANGE will achieve an overall MIBI adoption/preparation of 20% or more of the approximately 750 HSOs (*n* = 150), which Rogers [14] termed the “tipping point” and when reached may cause the rate of subsequent adoption/preparation to rapidly accelerate throughout the target audience. More realistically, however, MOTIVATE CHANGE will achieve MIBI adoption/preparation among only innovators and early adopters, which together represent the first 16% (2.5% innovators and 13.5% early adopters).

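### Adoption is presented as a four-month outcome, but access to everything that counts as adoption closes about 30 days after the first email

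*Protocol article*

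**What the plan says.** **Horizon.** The Methods paragraph of the abstract states: "Assessed 4-months post-dissemination, the primary dissemination outcome is organizational-level adoption/preparation of the intervention". The Discussion says the results may help training centers estimate "how much change occurs in the very short-term (i.e., one week) versus a longer period (i.e., four months", and it says this of both the exploration and the adoption/preparation phases.

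**What counts.** Under Outcomes, staff-level adoption is the "number of HSO staff who download the MIBI manual and/or enroll in the online asynchronous MI training". An HIV service organization (HSO) has adopted once one of its staff has done so.

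**When those actions are possible.** Under Distributing educational materials, "Phase I resources include the MIBI Manual for self-review and no-cost access to the online course". Staff who consent "gain access to Phase I resources for approximately thirty days from the time of the initial email invitation", and the enrolment route closes on the same clock: "Email recipients have approximately 30 days to engage with the study’s landing page and enroll in the study". The Control condition section gives the same expiry for control and immediate-exploration HSOs. The Exploration facilitation section says that a call does not move it: "Access to the training resources remains on the original schedule (i.e., access expires approximately thirty days from the date of the initial email invitation".

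**When the call comes.** Randomization follows a one-week run-in. The facilitator "will call the HSO within ~ 10 business days after randomization", makes up to three attempts, may leave a voicemail, and can schedule a call for another time. No last day is given for later attempts or scheduled calls.

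**The concern.** The stated time of the primary outcome and the period in which it can happen differ by about three months. After about day 30 neither qualifying action is open to an HSO that has not already taken it. A reader of the abstract or the Discussion would take the adoption rate as what four months of opportunity produces, when it reflects about one month.

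The facilitation strategy also has to act in what remains of that month after the run-in and the calling period. An HSO first spoken to close to expiry has little time to act, and one first spoken to after expiry has no access left. Both stay in the facilitation arm under intention to treat. A null result would then be hard to read: it could mean that the strategy does not work, or that some calls came too late to count.

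**Working it through.** The article gives no power calculation or other computed figure for this point, so the check is calendar arithmetic on its stated times.

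**Inputs**
- Day 0: the initial email, sent on a Tuesday (Distributing educational materials). The first was sent on 29 October 2024 (Trial status), which is a Tuesday.
- Randomization: after a one-week run-in, so day 7 at the earliest.
- First call: within about 10 business days of randomization.
- Expiry of landing page and Phase I access: about day 30.
- Four months from 29 October 2024: 28 February 2025, day 122.

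**Share of the horizon in which adoption can occur**
- From the first email: 30 / 122 = 25%.
- After randomization: 30 − 7 = 23 access days out of 122 − 7 = 115, and 23 / 115 = 20%.
- From about day 30 to day 122, 92 days, no new adoption can accrue in any group. The four-month survey cannot add adopting HSOs, because it goes only to staff already enrolled and enrolment has closed by then.
- Phase II access lasts 60 days, but it is not part of the adoption definition and comes after the Tour of MI course.

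**Access left at the first call**
- 10 business days after day 7 (5 November) is 19 November, day 21. It is day 22 if 11 November is treated as a holiday.
- Expiry is 28 November. Days left from day 21: 30 − 21 = 9, and 9 / 23 = 39% of the post-randomization access days.
- If randomization is carried out on days 7 to 10 (assumption), a call at 10 business days falls on days 21 to 24 and leaves 9 to 6 days.
- If a repeat or scheduled call comes 12 to 15 business days after randomization (assumption; the article gives no limit), it falls on days 23 to 31 and leaves 7 to −1 days.
- A call at 5 business days after a day-7 randomization falls on day 14 and leaves 16 days, so an early call is not squeezed.

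**The Discussion's contrast, by outcome**
- Adoption: the longer period available is about 30 days, so the contrast is one week versus about 30 days.
- Exploration: the outcome is opening either dissemination email. The expiry applies to the landing page and resources, and nothing in the article says that opens stop counting then. The four-month contrast is not ruled out here.

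**The case against.** **Assessed at four months need not mean at risk for four months.** The abstract can be read as saying when cumulative status is ascertained, and Outcomes takes status from the enrollment database and the four-month survey. This stands: a reader might infer that the abstract's statement is false, and the text does not support that. It does not rescue the Discussion, which treats four months as a period over which change occurs. The Strengths and limitations section also names four months as the follow-up limit and does not mention the 30-day closure.

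**The window is the same in both arms and was chosen openly.** This stands too. A reader might infer that the randomized comparison is biased. It is not: the expiry is identical, the analysis is by intention to treat, and the comparison validly estimates the strategy as specified, with fixed access.

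**Dilution is not shown.** A reader might infer that the effect is known to be attenuated, or by how much. The article reports no call dates, 10 business days is an upper bound, and the three attempts may all fall within it. The facilitator resends the email so that staff can act before expiry, which suggests that calls were meant to fall inside the window. Nine days can be enough to download a manual or enrol, since neither reading it nor finishing the course is required. What remains is a possibility of unknown size, mainly from scheduled calls and any late attempts.

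**Access could have been extended.** A reader might infer that the remedy is a later expiry. Trial status says the experiment ended on 14 May 2025, so that remedy is no longer available.

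**Conclusion.** The point holds in a limited form. On the stated access rules the primary outcome is adoption by about day 30, looked up at four months. It can accrue on about 25% of the nominal horizon, or about 20% of it after randomization, and the Discussion's one-week versus four-month contrast cannot be made for adoption. This rests on both qualifying actions requiring Phase I access, which the article says directly, and on the expiry having been applied as written. Both the 30 days and the 10 business days are approximate, so the day counts are too.

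On call timing, an on-schedule first call can leave about 9 access days, and nothing stated prevents a scheduled call from falling after expiry. Any HSO first reached then would tend to pull the estimated effect toward no difference. The number of such HSOs cannot be derived from the article, so no size is put on the attenuation. The calendar result is firm; the dilution is only a possibility that the trial's own call records can settle.

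**What to change.** 1. Reconcile the abstract, Outcomes and Discussion with the access rules: define the primary outcome as adoption by access expiry (about 30 days after the initial email), ascertained at four months.
2. In the Discussion, limit the contrast for adoption to one week versus about 30 days. Exploration need not be changed on this ground.
3. Add the 30-day closure to the limitations, beside the four-month follow-up limit.
4. Beside the intention-to-treat result, report for the facilitation arm the distribution of the interval from first completed call to expiry, and the share of HSOs first reached after expiry. Keep this descriptive; HSOs should not be removed from the primary analysis because of it.

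The cost is a few sentences and one small table, assuming that call dates were logged. Nothing in the conduct of the trial or in the randomized comparison changes. The gain is that the adoption rate carries its true time frame and a null result can be read against the time in which facilitation could act.
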